#### Secondary outcome measures

Secondary outcome measures will be the risk of falling, fall-related self-efficacy score, measures of balance, mobility and strength, health services use and difficulty with daily tasks. These outcome measures are described below.

**Fall-related self-efficacy** will be assessed with the *Falls Efficacy Scale International*[28], translated and adapted in its Brazilian version [29], which consists of a questionnaire with16 activities in which the participant rates, on a 4-point scale their degree of concern about the possibility of falling while carrying out the activities. It measures their degree of self-efficacy to avoid falling.

**Balance mobility and strength** will be measured by the: *Berg Balance Scale*[30-32], *Alternate Step test*[31], *Sit to stand Test*[33,34]*and Hand grip strength*[35,36]. The Berg Balance Scale consists of 14 common tasks involving static and dynamic balance, such as reaching, turning, moving, standing and getting up. Ability to perform the tasks is graded from 0 to 4, with an overall maximum score possible of 56 points, and higher scores indicating better balance. The *Alternate Step test*[31] requires the participant to stand in front of an 18-cm high step or stool and at a verbal command the participant taps the whole foot (shoes removed) onto the step, and alternates with the right and left feet, for a total of eight repetitions as quickly as possible. The time taken to complete the task is the score. The *Sit-to-stand test* will be used to primarily assess lower limb strength. There will be a pre-test which involves the patient moving from sitting in a chair to a standing position without the assistance of their hands. If the subject can perform this movement, they will be instructed to repeat the test, as quickly as possible, five times consecutively with their upper arms crossed over their chest. The time taken to perform this task will be recorded. *Hand Grip strength* will be assessed using a portable hand dynamometer (SAEHAN® model SH5001). The participant will be seated with their shoulder in a neutral position and their elbow flexed at 90°.Three attempts will be performed alternately in each hand; the mean of the three measures will be recorded.

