**Fall risk** will be assessed using the *QuickScreen Clinical Falls Risk Assessment*[37], a validated instrument consisting of five physical performance items, two questions about medications and one about previous falls. An individual’s estimated fall risk will be considered to have decreased if, upon retest, they have moved down to the next level in the risk categories proposed by Tiedemann et al. [37]. The risk categories and their associated probabilities of future falls are as follows: for 0–1 QuickScreen items, the probability of falling is 7%, for 2–3 items the probability of falling is 13%, for 4–5 items the probability of falling is 27% and for 6 or more items the probability of falling is 49%.

**The level of *****difficulty with daily tasks*** will be assessed using the Brazilian OARS Multidimensional Functional Assessment Questionnaire (BOMFAQ) adapted from the Older Americans Resources and Services (OARS) [38] instrument that measures self-reported difficulty while performing 15 daily activity tasks: eight activities of daily living : lying down and getting up from bed, eating, combing hair, dressing, bathing, walking on a uneven surface, getting to the toilet in time, cutting toenails and seven instrumental activities of daily living: taking medications, climbing stairs, walking near home, preparing meals, taking public transport, shopping and cleaning the house, hierarchically organized. The number of activities performed with difficulty will be summed and categorized as follows: 0, 1 to 3, 4–6 or 7 or more activities.

**Services use** will be measured by the number of fall-related visits to emergency departments and hospitalisations (frequency and duration) per participant.

**Compliance** with the home exercise program (frequency and duration) will be recorded in a home exercise diary. Adverse side effects will be measured with an adverse events form, including stiffness, pain, fatigue, etc. At the end of the follow-up period participants will be asked to identify reasons for non-adherence on the home-based exercise program.

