### Statistical analysis

The primary analyses will be conducted using the intention-to-treat principle. Fall data will be analysed using all randomised participants until they have died or have withdrawn from the study. Demographic and clinical characteristics at baseline will be summarized with descriptive statistics. The incidence of falls with 95% confidence intervals (CIs) in the two groups (intervention group and control group) will be calculated and compared using negative binomial regression analysis. The proportion of fallers in the two groups will be compared with the relative risk statistic. General linear models will be used to assess the effect of group allocation on the continuously-scored secondary outcome measures after adjusting for baseline scores. Logistic regression models will be used to compare groups on dichotomous outcome measures. Interactions between subgroup variables (past falls and mobility-related disability) and group allocation will be tested, and in the case of a significant interaction, the comparison between the intervention group and control group will be reported within the subgroups. Statistical analyses will be undertaken using the SPSS and Stata software packages. P < .05 will be considered statistically significant.

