## Discussion

There is a substantial amount of evidence that falls in older adults can be reduced by different interventions in multiple settings. However, interventions in developing countries with limited resources are scarce and yet to be fully investigated.

Thus, we aim to develop a program which is feasible in terms of intensity and characteristics, combining specific on-site approaches during a short period of time with home-based exercises. We believe that these strategies, if proved to be effective, could be implemented by a small team of primary health care professionals with a small amount of training.

This study will also help to understand home-based exercise adherence predictors in this population. The proposed sub-group analyses may also identify specific participant groups that are most likely to gain benefit from the intervention. Furthermore, secondary outcomes analyses will determine if there is any significant improvement in physical functioning and disability in older people as a result of the intervention, which to our knowledge has not been investigated previously with older Brazilian adults over a 12 month follow-up period.

In summary, this study is the first randomised controlled trial of a multifactorial falls prevention program to be conducted among Brazilian older adults. The pragmatic design of the intervention will ensure that study results can be implemented into clinical practice with minimal effort. If proven effective, this fall prevention program will benefit older adults and assist health care practitioners and policy makers to make better choices concerning falls prevention interventions.

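### The daily-task outcome is scored in four uneven bands that hide most one-task changes and match neither planned model; the 0–15 sum should be the analysed outcome

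*Protocol article*

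**What the plan says.** Under Secondary outcome measures, the Protocol article lists "health services use and difficulty with daily tasks" among the secondary outcomes. The scale is the BOMFAQ, an "instrument that measures self-reported difficulty while performing 15 daily activity tasks", eight of them basic and seven instrumental activities. Its scoring is given in one sentence: "The number of activities performed with difficulty will be summed and categorized as follows", with the bands "0, 1 to 3, 4–6 or 7 or more activities". No other scoring is stated.

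The Statistical analysis section names two kinds of model for secondary outcomes. The first is for continuous scores: "General linear models will be used to assess the effect of group allocation on the continuously-scored secondary outcome measures after adjusting for baseline scores". The second is for binary ones: "Logistic regression models will be used to compare groups on dichotomous outcome measures". No ordinal model is named.

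The other banded secondary outcome, QuickScreen fall risk, does have a rule that makes it binary: a participant's "estimated fall risk will be considered to have decreased if, upon retest, they have moved down to the next level in the risk categories".

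The Discussion says what the secondary analyses are for: "secondary outcomes analyses will determine if there is any significant improvement in physical functioning and disability in older people".

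**The concern.** The sum already exists when the bands are formed, so banding discards information that has been collected. The cut-points are also uneven. A participant who goes from difficulty with 15 tasks to difficulty with 7 is recorded as unchanged, while one who goes from 7 to 6, or from 1 to 0, is recorded as improved.

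Two things are at stake. The first is sensitivity: this is the only listed outcome that records difficulty with daily activities, and the Discussion relies on the secondary analyses to show whether disability improves. The second is clarity: as scored, the outcome has no matching model in the article, so the choice of analysed form is left open.

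**Working it through.** **No planned figure to reproduce.** The article gives no effect size, variance or power for this outcome. Its 612 participants (306 per group) are sized on the rate of falls.

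**Step 1: band widths.** The sum of 15 tasks has 16 possible values.

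| Band | Scores | Number of scores |
|---|---|---|
| 0 | 0 | 1 |
| 1–3 | 1, 2, 3 | 3 |
| 4–6 | 4, 5, 6 | 3 |
| 7 or more | 7 to 15 | 9 |

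1 + 3 + 3 + 9 = 16.

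**Step 2: which one-task improvements register.** There are 15, from 1→0 up to 15→14. Three cross a boundary: 1→0, 4→3 and 7→6. The other 12 do not: 2 within 1–3, 2 within 4–6 and 8 within 7–15 (2 + 2 + 8 = 12). This needs no assumption.

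**Step 3: match to the planned models.** Four ordered levels are not dichotomous, and band codes 0 to 3 are not a continuous score. QuickScreen becomes binary by its stated rule, so logistic regression applies to it. The daily-task outcome has no such rule.

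**Step 4: power, sum against bands.** All inputs here are assumed: 260 per arm analysed (260/306 = 85%), a beta-binomial 0–15 score, a baseline-to-follow-up correlation of 0.7, a latent effect of 0.18 SD, and a baseline-adjusted linear model for both forms. The table shows two sets of simulations.

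| Mean tasks | Set A: sum | Set A: bands | Set B: sum | Set B: bands |
|---|---|---|---|---|
| 2 | 62–68% | 62–67% | 57–67% | 58–65% |
| 3 | 68–75% | 67–70% | 66–73% | 65–67% |
| 5 | 78–79% | 66–68% | 73–79% | 66–70% |
| 7 | 77–82% | 60–63% | 78–81% | 60–65% |

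Set B varies the beta-binomial precision over 2, 3 and 6. With precision 3, the share scoring 7 or more is about 16% at mean 3 and 33% at mean 5; at mean 7 it is about half. The loss is therefore about nil at mean 2, a few points at mean 3, roughly 10 points at mean 5, and up to about 20 points at mean 7.

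**Step 5: a second measure of the loss.** Relative efficiency is the squared standardised group difference for the band score divided by that for the sum. With precision 3, a shift of one task between groups and no baseline adjustment, it is 1.13 at mean 3, 1.05 at mean 4, 0.98 at mean 5, 0.92 at mean 6 and 0.75 at mean 8. The direction agrees with step 4, but the loss starts at higher means. For comparison, power of 80% for the sum and 68% for the bands corresponds to ((1.96 + 0.47)/(1.96 + 0.84))² = (2.43/2.80)² ≈ 0.75. So at mean 5 the answer runs from almost no loss to about a quarter of the information, depending on how the effect is modelled.

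**Step 6: within-person change.** Under the step 4 assumptions, 28–41% of participants who improve by at least one task stay in the same band at means of 3 to 5, and about half do at mean 7.

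**The case against.** Four points can be made for the plan.

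*The sum is formed first.* The article does not say that the bands are the analysed variable, and a summed count could pass as a continuously scored measure. This stands in part. The fix is compatible with the present text, and a reader who infers that the plan forces a linear model on band codes or a collapse to yes/no goes beyond it. But the bands are the only scoring stated, so the text as written points to the inferior form.

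*Assigning a model to each secondary outcome belongs in the analysis plan.* Taken alone, the missing ordinal model would be no finding in a condensed article. The point rests on what the article does state, namely a banded outcome beside two model types that do not cover it.

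*The loss is assumption-driven.* This stands. A reader might also quote much lower powers, in the range of 27–46%, by testing whether participants moved down a band or scored 7 or more. The article sets the first rule for QuickScreen only and the second nowhere, so those figures cannot be charged to this plan.

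*The sample may seldom reach the top band.* Participants live in the community, must attend weekly for 12 weeks, and are excluded if they cannot stand or have severe stroke impairment or progressive neurological disease. A change from 15 to 7 is therefore an extreme example. How full the top band will be cannot be told from the document. Nor can it be checked whether the bands are the instrument's customary ones; if they are, that supports tabulating them but does not make them sensitive to change.

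**Conclusion.** The point holds as a free improvement to a secondary outcome. That the bands are uneven, that 12 of 15 one-task improvements go unseen, and that the form matches neither named model are certain from the text. The cost in power is not: it runs from about 0 to about 20 percentage points under the assumed distributions, and it is material only if a sizeable share of participants score 7 or more. A yes/no collapse would cost more, but the plan does not prescribe one. The primary fall outcomes and the sample size are untouched, and no collected data are lost.

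**What to change.** State that the analysed outcome is the 0–15 sum of tasks done with difficulty, compared between groups with the baseline-adjusted general linear model already in the Statistical analysis section, and that the four bands are for descriptive tables only. Naming an ordinal model for the bands would settle the mismatch but not recover the information: at a mean of 5 tasks, a proportional-odds model on the bands gave about the same power (68%) as a linear model on the band codes.

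The cost is one sentence. Items, visits and forms stay as they are. The article reports that the trial is still recruiting, so the choice can be recorded before outcome data by group are seen.

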### Baseline assessment of clinical fall risk factors

Individual clinical fall risk factors will be established through questions about urinary incontinence, diabetes, alcohol consumption, physical activity level, medication use and the number of hospitalisations or emergency department visits during the past year. Physical examination will be undertaken by trained physicians and will consist of:

*Postural hypotension* identified by assessment of blood pressure after 5 minutes in the supine position and after 2 minutes in the standing position. Abnormality is defined as a difference of 20 mmHg or a 20% decrease in systolic BP with or without symptoms, or a reduction in the diastolic BP of 10 mmHg. *Vibratory perception* will be assessed using a vibrating tuning fork of 128Hz applied over the bony part of the dorsal distal phalanx of the hallux*. Cognition* will be assessed with the Mini Mental State Examination (MMSE) [39]. *Depressive Symptoms* will be assessed by the Geriatric Depression Scale (GDS) translated and validated in Brazil. The short version has 15 questions with a yes/no response concerning the participant’s emotional state in the week preceding the assessment. A score of 6 or greater indicates a depressed mood [40,41]. *Visual acuity* will be measured using a directional Table E or Snellen (Snellen-E chart), which is a standardised measure of vision, conducted at a distance of five metres. As the intention is to measure functional vision, the participants will be allowed to wear their usual corrective lenses, and both eyes will be evaluated simultaneously. Values below 0.3 will be considered to indicate impaired vision. *Nutritional Status* will be measured with Body Mass Index (BMI) and calf circumference. The following BMI classifications will be used: BMI < 22 kg/ m^2^ = underweight, between 22 and 27 kg/ m^2^ = normal weight, >27 kg/ m^2^ = obese [42].

### Sample size calculation

A total of 612 participants (306 per group) will provide 80% power to detect as significant, at the 5% level, a 30% lower rate of falls (i.e. the primary outcome measure) for intervention group participants compared with control participants (i.e., IRR = 0.70). For the sample size calculation we used the gennbreg command in Stata and coefficients from previous studies: alpha (a measure of over-dispersion in the negative binomial regression model) was assumed to be 0.76 based on data from a previous trial [43]. We assumed the control group rate of falls would be 1 fall per person over the 12-month follow-up period. An average follow-up period of 11 months (rather than the planned 12 months) was used in these calculations to account for loss to follow-up.

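### The listed sample size inputs give about 86% power at 306 per group, not 80%; for 80% they need about 258 per group

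*Protocol article*

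**What the plan says.** The Sample size calculation section of the protocol article makes one power statement: "A total of 612 participants (306 per group) will provide 80% power to detect as significant, at the 5% level", for a 30% reduction in the fall rate (rate ratio 0.70). It then lists what went into the calculation:

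- Control rate: "We assumed the control group rate of falls would be 1 fall per person over the 12-month follow-up period".
- Over-dispersion: "alpha (a measure of over-dispersion in the negative binomial regression model) was assumed to be 0.76", taken from an earlier trial.
- Follow-up: "An average follow-up period of 11 months (rather than the planned 12 months) was used in these calculations". The section gives loss to follow-up as the reason for the shorter figure.
- Tool: the Stata command gennbreg.

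The Statistical analysis section names negative binomial regression for the comparison of fall rates and a significance threshold of 0.05. The sample size section mentions no further dropout inflation, clustering allowance, split of the significance level or rounding margin.

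**The concern.** The section prints every quantity that the usual negative binomial calculation needs, so its result can be checked directly, and it does not come out. The listed inputs lead to a clearly smaller number than 306 per group or, read the other way, to clearly more than 80% power at 306.

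This section is the article's only justification for enrolling 612 people. As printed, a reader cannot tell whether the power is understated or whether one of the listed inputs is not the one used. The two cases differ in practice. In the first, the trial has about 6 points of power in hand. In the second, that margin has already been used by an assumption that is not on the page.

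**Working it through.** **Inputs**, all from the Sample size calculation section except where noted:

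- control rate r0 = 1 fall per person-year; intervention rate r1 = 0.70 × 1 = 0.70
- over-dispersion k = 0.76 (variance = μ + kμ²)
- mean follow-up t = 11/12 = 0.9167 year
- 1:1 allocation, 306 per group
- significance level 5%. Sidedness is not stated; two-sided is my assumption (z = 1.960), and one-sided is tried below. For 80% power, z = 0.842.

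**Step 1. Attempt to reproduce 306 per group.** For a Wald test of the log rate ratio:

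n per group = (z_α + z_power)² × V / (ln IRR)², with V = 1/(t·r0) + 1/(t·r1) + 2k.

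- V = 1/0.9167 + 1/0.6417 + 2 × 0.76 = 1.091 + 1.558 + 1.520 = 4.169
- (ln 0.70)² = 0.1272
- n = 7.849 × 4.169 / 0.1272 = 257.2, so 258 per group, 516 in total

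The stated 306 is not reproduced. It exceeds 258 by 48 per group, and 306/257.2 = 1.19.

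**Step 2. Power at 306 per group.**

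Power = Φ(√(306 × 0.1272 / 4.169) − 1.960) = Φ(3.056 − 1.960) = Φ(1.096) = 86.3%.

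**Step 3. Simulation.** Data were generated from the negative binomial model with the same inputs, fitted by maximum likelihood and tested by Wald. With 10,000 runs per setting, power was 87.0% at 306 per group and 80.4% at 258. This agrees with the formula.

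**Step 4. Does the pattern of follow-up matter?** A mean of 11 months can arise in different ways. For participants with varying t, the information per participant in a group with rate r is the average of r·t/(1 + k·r·t), and V is the sum of the two reciprocals.

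- One sixth leave uniformly over the year and the rest complete it (mean 5/6 + 1/12 = 11/12): information 0.5297 (control) and 0.4242 (intervention), V = 4.245, n = 262, power at 306 = 85.7%.
- One twelfth contribute no data and the rest complete the year: V = 3.949 × 12/11 = 4.308, n = 266, power at 306 = 85.2%.

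Either pattern costs about one point of power or less.

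**Step 5. Other conventions applied to the same inputs.**

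| Variant | n per group for 80% | Power at 306 |
|---|---|---|
| As in steps 1 and 2 | 258 | 86.3% |
| Null variance from pooled rate | 254 | – |
| Null variance from control rate | 237 | – |
| Variance on the mean-difference scale | 261 | 85.9% |
| Full 12 months | 244 | 88.1% |
| One-sided 5% | 203 | 92.1% |

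None comes near 306. One-sided testing and full follow-up both widen the gap.

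**Step 6. What would give 306 at 80%?** Changing one input at a time, V would have to be 306 × 0.1272 / 7.849 = 4.960, which needs over-dispersion of about 1.16 or a control rate of about 0.77. Alternatively the rate ratio would have to be about 0.722. Each differs from the printed value. Figures close to 306 also come from further dropout of 15 to 16% on top of the 11 months (258/0.85 = 304; 258/0.84 = 307), from 20% dropout with the full 12 months (244/0.80 = 305), or from a two-sided level of 0.025 (n = 312; power 79.2% at 306). The section states none of these.

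**The case against.** The strongest reply is that this is a journal article. A further allowance behind 306 may stand in the full protocol, and what an article leaves out for brevity is not an error. The section also speaks of coefficients from previous studies in the plural but ties only the over-dispersion to one, so the printed list may be incomplete. This has some force: it is why the cause of the gap cannot be named. It does not rescue the statement. The section reads as a complete calculation, gives the 11 months as its account of loss to follow-up, and attaches 80% to 306 on that basis. The printed figures disagree with each other, which is different from a detail left out.

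A second reply is that the figure came from a simulation command and carries simulation error. With a true power of 86.3%, the standard error is √(0.863 × 0.137/100) = 3.4 points at 100 replicates, so a reading of 80% would be possible with about that many. At 500 replicates it is 1.5 points and the gap is about 4 standard errors; at 1,000 it is 1.1 points and the gap is nearly 6. The number of replicates is not reported.

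A third reply is that the error is harmless, because the trial exceeds its target. That stands in full and limits the weight of the point.

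Two stronger readings are tempting. A reader might infer that the article presents 612 as the minimum needed; it says only that 612 provides 80% power. A reader might also take the surplus of 1.19 as a margin reserved for correlation within the exercise groups of 10 to 12. Neither the sample size nor the analysis section mentions clustering, so that would be a rationale supplied after the fact.

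**Conclusion.** The point holds. Under the listed inputs and a two-sided 5% test, 80% power needs about 258 per group (516 in total), and 306 per group gives about 86% (85.7% with uniform departure of one sixth of participants). The stated pairing of 306 per group with 80% is off by 48 per group, or about 6 power points, and no usual choice of sidedness, follow-up pattern or variance form closes the gap.

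This is a defect of reporting and reproducibility. It does not show that the trial is too small: under its own scenario it has more power than it claims. Nor does it show which input is wrong, or that loss to follow-up was counted twice. An extra 15 to 16% for dropout would fit the arithmetic, but so would several other unstated changes, and the article does not favour any of them.

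**What to change.** Restate the power sentence in the Sample size calculation section in one of two ways:

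1. If the listed inputs are the ones used, say that 306 per group gives about 86% power for a rate ratio of 0.70 at the two-sided 5% level.
2. If a different input or a further allowance was actually used to reach 306, state its value and correct the list so that 80% can be reproduced from it.

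In either case, state the sidedness. Do not add a clustering rationale unless it was the actual basis of the calculation. The cost is one corrected sentence, plus a look at the original Stata run to see which case applies. Enrolment does not change.
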